### Sample size {14}

PASS11 software was used to calculate the sample size. According to the previous literature [65, 66], which includes the results of PDQ-39 in individuals with Parkinson’s disease, and in combination with this experiment, we designed a ratio of 1:1 between the tACS + MIRT group and Sham-tACS + MIRT group. The statistical power was set at 0.9, with a significance level (α) of 0.05. Based on these parameters, the required sample size for each group was calculated as 27. Considering an attrition rate of 10%, it was determined that each group would need a total of 30 patients, resulting in a combined total of 60 patients.

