### Procedure for unblinding if needed {17b}

When encountering serious adverse events that necessitate immediate unblinding, the scientific research management department head, data management department project leader, and statistician will jointly perform the unblinding process and meticulously document it. Unblinding will solely disclose the treatment received by a patient through a randomized number, without impacting the blinding of other participants. It will not be involved in efficacy analyses but will be included in safety analyses.

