## Data collection and management

### Plans for assessment and collection of outcomes {18a}

The following data will be collected at baseline: gender, age, occupation, educational level, current medication status, and detailed physical and neurological examinations. Inclusion and exclusion criteria will be evaluated. PDQ-39 assessments will be conducted at T0, T2, T3, and T4. MDS-UPDRS III [49, 55], Mini-BES test [50, 56], 6MWT [51, 57], NMSS [52, 58], MoCA [53, 59], and HAMD, as well as other motor symptom scales and non-motor symptom scales, will be assessed at T0, T1, T2, T3, and T4 respectively. MRI and EEG scans will be evaluated at T0 and T1. Levodopa equivalent daily dose (LEDD) data will be collected at T0, T1, T2, T3, and T4. All these assessments will be conducted in a double-blind manner by raters who were unaware of the treatment administered to the patients. At T0 and T1, various safety indicators including blood routine, urine routine, stool routine, liver and kidney function tests, electrocardiogram readings, and other relevant parameters will be evaluated. Any adverse events occurring during the study will be documented. Participants will be asked for their consent regarding the use of their data if they choose to withdraw from the trial. Additionally, participants must obtain permission from the research team to share their pertinent information with university personnel involved in the study or relevant regulatory authorities. Prior to commencing the study, investigators will undergo standardized training on data collection strategies as well as guidelines for utilizing different scales to assess outcomes. Throughout the trial period, professionally trained researchers will collect data to ensure impartiality. In case subjects experience an “on–off” phenomenon during treatment response fluctuations; separate data collection sessions will take place during both “on” and “off” periods for subsequent comparison.

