### Methods in analysis to handle protocol non-adherence and any statistical methods to handle missing data {20c}

The intention-to-treat (ITT) analysis will be the primary analysis of this study, with per-protocol (PP) analysis as a secondary analysis in case patients were unable to receive the intervention due to issues related to the intervention itself, such as adverse effects, difficult administration, or adherence problems. Missing data will be handled using the last observation carried forward (LOCF) method. Sensitivity analyses will be conducted if there are imbalanced losses to follow up or excessive attrition.

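### Patients unblinded for a serious adverse event are excluded from the efficacy analyses, which contradicts the intention-to-treat primary analysis

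*Protocol article*

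**What the plan says.** Section 20c (non-adherence and missing data) sets the analysis population: "The intention-to-treat (ITT) analysis will be the primary analysis of this study". A per-protocol analysis is secondary, for patients who could not receive the intervention "due to issues related to the intervention itself, such as adverse effects, difficult administration, or adherence problems". The same section adds: "Missing data will be handled using the last observation carried forward (LOCF) method".

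Section 17b (unblinding) covers emergencies. It applies "When encountering serious adverse events that necessitate immediate unblinding", and the code is then broken for that one patient. It ends: "It will not be involved in efficacy analyses but will be included in safety analyses". No exception to intention-to-treat is stated in either section.

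Two other places bear on the point. The dropping criteria list patients who stop treatment, for whatever reason, separately from those who revoke consent. They do not say whether these patients are still followed or analysed. Section 18a gives the visits for the primary outcome: "PDQ-39 assessments will be conducted at T0, T2, T3, and T4". There is no PDQ-39 at the end of treatment (T1).

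**The concern.** Intention-to-treat keeps every randomised patient in the comparison so that nothing after randomisation can decide who is counted. Section 17b lets a serious adverse event decide it. The active arm receives 15 mA and the sham arm no current, and the adverse-event section (22) itself names seizures, headaches and site irritation pain as possible events. The events that lead to unblinding could therefore differ between arms, and the patients removed may have a different quality-of-life course from those who stay.

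If 17b is followed, the primary result is not an intention-to-treat result, whatever its label. If the conflict is left open, it will have to be settled for a patient whose allocation is already known.

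A secondary concern is the dropping criteria. If being dropped ends follow-up, the intention-to-treat analysis keeps the patient in name but has no PDQ-39 value after baseline for that patient.

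**Working it through.** **1. The two rules side by side.** The pronoun that opens the last sentence of 17b is loose: grammatically it could refer to the act of unblinding. But an act cannot be counted in a safety analysis, whereas a patient's data can. The only sensible reading is that the unblinded patient's data count for safety and not for efficacy. Section 20c counts the same patient in the primary efficacy analysis. Its place for departures caused by adverse effects is the secondary per-protocol analysis, not removal from efficacy altogether. The two rules are incompatible.

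**2. The plan's own numbers.** Section 14 gives 27 per group before attrition, 10% attrition and 30 per group. Check: 27 / (1 − 0.10) = 30, which reproduces. The 27 cannot be checked because the article gives no difference or SD. Solving backwards for 27 per group, power 0.90 and two-sided α 0.05 (sidedness is not stated, so this is an assumption), a t-test implies a standardised effect of 0.90.

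**3. Size in PDQ-39 points (assumed values).** Let k of the 30 patients in one arm be removed, with a mean PDQ-39 outcome G points worse than the rest of that arm. The arm mean then shifts by (k/30) × G. The yardstick is the 4.72-point improvement threshold in section 12. Baseline adjustment is ignored.

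| k | G = 5 | G = 10 |
|---|---|---|
| 1 | 0.17 (4%) | 0.33 (7%) |
| 2 | 0.33 (7%) | 0.67 (14%) |
| 3 | 0.50 (11%) | 1.00 (21%) |

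For example, 1/30 × 5 = 0.17 and 0.17/4.72 = 4%; 3/30 × 10 = 1.00 and 1.00/4.72 = 21%.

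**4. Size in SD units (assumed values).** Let g be the gap in SD between the removed patients and the full-arm mean. The retained mean shifts by k × g / (30 − k).
- k = 1, g = 0.5: 0.5/29 = 0.02 SD, 2% of the implied effect of 0.90.
- k = 2, g = 1.0: 2/28 = 0.07 SD, 8%.
- k = 3, g = 1.5: 4.5/27 = 0.17 SD, 19%.

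With no true difference and all removals from one arm, the two-sided type I error rises from 0.05 to 0.051, 0.058 and 0.095 in these three cases.

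**5. Power.** Starting from 27 evaluable per group, losing 1, 2 or 3 more from one arm lowers power from 0.90 to 0.894, 0.888 or 0.881. The issue is bias, not power.

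**6. Direction.** Higher PDQ-39 scores are worse, so removing patients who do worse improves that arm's mean. This flatters active stimulation if the events fall in the active arm and flatters sham if they fall there. Similar removals from both arms would largely cancel. If the removed patients did better than the rest, the sign would reverse.

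**7. Dropping criteria.** Treatment runs on days 3 to 12 and the first PDQ-39 after baseline is at T2, 4 weeks after the intervention. A patient who stops during treatment and is not followed has only T0. Carrying T0 forward gives a change of T0 − T0 = 0 at T2, T3 and T4.

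**The case against.** The rule in 17b is narrow. It does not cover every serious adverse event, only those that require immediate unblinding, and three officials must act jointly. Few cases are likely among 60 patients, and with one patient and a 5-point gap the shift is under 4% of the threshold. All of this stands, and it limits the size of the problem. It does not remove the contradiction over who is in the primary analysis.

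A reader might go further on three counts, and the document does not support any of them.

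- **That the excluded events are treatment-related.** Section 17b does not require relatedness. They are possibly treatment-related, no more.
- **That the bias favours active stimulation.** This needs the events to cluster in the active arm and those patients to do worse. The article gives no event rates by arm.
- **That treatment discontinuers are also removed from the intention-to-treat set.** The dropping criteria do not say so. Section 20c points the other way: a separate per-protocol analysis for patients who could not receive the intervention, and carrying values forward, make sense only if such patients remain in the main analysis. Nor would a zero change for them clearly help the active arm. The Discussion expects MIRT, which both arms receive, to improve quality of life, so a zero would tend to count against the arm with more discontinuers.

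How far a dropped patient is followed could be a detail that a condensed article leaves out. The dropping criteria are therefore a matter for clarification, not a second contradiction.

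**Conclusion.** The contradiction between 17b and 20c holds on the text alone. Following 17b would make a post-randomisation exclusion from the primary efficacy comparison, based on events that are possibly treatment-related and may differ between arms.

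The numerical effect is probably modest. The calculated shifts assume that all removals come from one arm and that the removed patients are worse by the stated gaps. Neither the number of such patients nor their outcomes can be taken from the article, and the direction is not established. The upper end of the range is not trivial: it nearly doubles the false-positive rate.

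This should be fixed, but as a correction of wording for a rare event rather than as a defect that undermines the trial. The dropping criteria need to be reconciled with 20c, on the condition stated: they matter only if being dropped ends follow-up.

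**What to change.** - **Section 17b:** delete the exclusion from efficacy. State that unblinded patients stay in the intention-to-treat set as randomised, and that any analysis without them is per-protocol or a sensitivity analysis.
- **Dropping criteria:** state that patients who stop study treatment but have not withdrawn consent to follow-up are still invited to the T1 to T4 assessments and analysed as randomised. Only withdrawal of consent to follow-up ends data collection.

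The cost is one sentence in each place, made in one amendment and before any allocation is revealed to the analysts, plus a small effort to keep inviting discontinuers to visits that are already scheduled. The sample size stays at 30 per group, 60 in total. Nothing changes in dosing, in when treatment is stopped or in when unblinding is allowed.

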## Data collection and management

### Plans for assessment and collection of outcomes {18a}

The following data will be collected at baseline: gender, age, occupation, educational level, current medication status, and detailed physical and neurological examinations. Inclusion and exclusion criteria will be evaluated. PDQ-39 assessments will be conducted at T0, T2, T3, and T4. MDS-UPDRS III [49, 55], Mini-BES test [50, 56], 6MWT [51, 57], NMSS [52, 58], MoCA [53, 59], and HAMD, as well as other motor symptom scales and non-motor symptom scales, will be assessed at T0, T1, T2, T3, and T4 respectively. MRI and EEG scans will be evaluated at T0 and T1. Levodopa equivalent daily dose (LEDD) data will be collected at T0, T1, T2, T3, and T4. All these assessments will be conducted in a double-blind manner by raters who were unaware of the treatment administered to the patients. At T0 and T1, various safety indicators including blood routine, urine routine, stool routine, liver and kidney function tests, electrocardiogram readings, and other relevant parameters will be evaluated. Any adverse events occurring during the study will be documented. Participants will be asked for their consent regarding the use of their data if they choose to withdraw from the trial. Additionally, participants must obtain permission from the research team to share their pertinent information with university personnel involved in the study or relevant regulatory authorities. Prior to commencing the study, investigators will undergo standardized training on data collection strategies as well as guidelines for utilizing different scales to assess outcomes. Throughout the trial period, professionally trained researchers will collect data to ensure impartiality. In case subjects experience an “on–off” phenomenon during treatment response fluctuations; separate data collection sessions will take place during both “on” and “off” periods for subsequent comparison.

### Plans to promote participant retention and complete follow-up {18b}

To minimize dropout rates, participants will be reminded to attend all interventions and assessments. Participants and their caregivers will receive two telephone reminders (1 week and 1 day) prior to interventions and assessments. A dedicated hotline will be provided to offer assistance to participants and their caregivers regarding any inquiries or concerns.

### Data management {19}

Based on the clinical research data platform of Parkinson Medical Center, Beijing Rehabilitation Hospital, the EDC system will be utilized for data entry and management. The task of data entry will be performed by trained data collectors. Participant information will be securely stored in the EDC system, accessible to researchers through password authentication. Rigorous checks will ensure the completeness of case report forms and consistency between coding and subjects screened for enrollment. Data validation procedures will be implemented upon entry into the EDC system, with subsequent review of original cases based on these results. The final dataset will be exported as an Excel spreadsheet (Microsoft, Redmond, WA, USA). [name] is responsible for conducting interim analysis while making a final decision regarding trial suspension based on these interim results. Access to the finalized trial dataset will only be granted to authorized researchers.

### Confidentiality {27}

The privacy of all participants will be safeguarded by assigning their information a unique trial identification code, and the study data will be securely stored in a password-protected file accessible only to the data manager of the research team.

### Plans for collection, laboratory evaluation, and storage of biological specimens for genetic or molecular analysis in this trial/future use {33}

We will obtain informed consent from the patient and collect biological samples, including blood, urine, feces, and saliva, for molecular biology analysis at T0 and T1. A rigorous verification process with a double-signing system will be implemented for each sample to ensure timely acceptance and thorough examination. Prior to centrifugation, the staff will conduct a comprehensive review of the subject’s name, hospitalization number, bed number, and project details. Furthermore, specimens will be uniformly stored in standardized conditions at designated locations within clearly labeled specimen boxes.

## Statistical methods

### Statistical methods for primary and secondary outcomes {20a}

SPSS v27.0 software (SPSS Inc., Chicago, IL, USA) will be used for data processing and analysis. Demographic and baseline characteristics of the two groups will be described and analyzed to assess comparability. The PDQ-39 will serve as the primary outcome measure, and an analysis of covariance (ANOVA) model will be employed to estimate the adjusted means of patients’ quality-of-life scores (LSmeans), accounting for baseline differences, as well as calculate 95% confidence intervals for the difference in adjusted means. The count data in the secondary outcome indicators are described by frequency counts. The measurement data are tested for normality using the Shapiro–Wilk method and expressed as mean ± standard deviation if they follow a normal distribution. For non-normally distributed data, they will be described using (P25, P75). Between-group comparisons of motor function, non-motor function-related scale scores, and other secondary indicators between the two groups will be analyzed using appropriate methods based on the type of indicator. Component comparisons such as quantitative information will be analyzed using analysis of variance or Wilcoxon rank sum test. Categorical data will be analyzed by chi-square test or exact probability method, while hierarchical information will be assessed through rank sum Wilcoxon test or CMH test. The significance level for each test will be set at *P* < 0.05.

The MRI pre-processing will be conducted using the data processing assistant for Rs-fMRI, which operates in conjunction with the statistical parametric mapping software (SPM82). Subsequently, the EEG data will undergo offline processing through MATLAB software scripts and the EEGLAB toolbox.

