#### Secondary outcome

The secondary outcome will encompass changes in motor symptom scales such as the third part of the Movement Disorders-Unified Parkinson’s Disease Rating Scale (MDS-UPDRS III) [49], Mini-balance evaluation systems test (Mini-BES Test) [50], and 6-min walking test (6MWT) [51] from T0 to T1, T2, T3, and T4. Additionally, alterations in non-motor symptom scales such as non-motor symptoms scale (NMSS) [52], Montreal cognitive assessment (MoCA) [53], and Hamilton depression scale (HAMD) [54] from T0 to T2, T3, and T4 will be evaluated.

MDS-UPDRS III comprises of 18 items designed to evaluate motor function in individuals with Parkinson’s disease (PWP). The Chinese version of the MDS-UPDRS III demonstrates excellent reliability and validity, exhibiting a strong correlation with the conventional UPDRS [55].Mini-BES test is utilized for assessing gait and postural stability. This scale has demonstrated excellent inter-rater reliability (intraclass correlation coefficient (ICC) > 0.95) as well as high test-retest reliability (ICC > 0.95) [56].6MWT measures the distance that a patient can quickly walk on a flat, hard surface within 6 min. We used the validated Chinese version which has shown a very high inter-rater correlation coefficient (ICC = 0:99) [57].NMSS allows quantitative evaluation of NMS of PD. The Chinese version of the NMSS can be considered a comprehensive, useful measure for NMS evaluation in Chinese PWP (Cronbach’s coefficient = 0.89, ICC = 0.99) [58].MoCA is a screening tool for mild cognitive impairment. The reliability of the Chinese version of MoCA has been proven in the clinic [59].HAMD will be utilized for the evaluation of a patient’s anxiety and depression levels. Its Chinese version has been empirically validated as a reliable and valid assessment tool [60].

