### Methods for additional analyses (e.g., subgroup analyses) {20b}

In case of baseline differences between the 2 groups (tACS + MIRT and sham-tACS + MIRT), statistical analyses will be adjusted to take into account specific variables that may have influenced the results for subgroup analysis (e.g., LEDD, illness duration, and age). The post hoc analyses will also be performed with Bonferroni corrected *t*-tests to examine the improvements in all outcome variables through comparisons across different assessment time points. Additionally, distinct exploratory analyses will be conducted for EEG and functional MRI data in order to gain a more comprehensive understanding of the impact of tACS intervention on brain plasticity.

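### The plan names both ANOVA and the Wilcoxon rank sum test for the quantitative secondary scales without a rule for choosing, so the choice can follow the data and differ between visits of one scale

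*Protocol article*

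**What the plan says.** All of the relevant text is in the Protocol article, mainly under Statistical methods for primary and secondary outcomes {20a}.

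- **Primary outcome.** PDQ-39 has one named analysis, a covariance model that accounts for baseline, from which the authors will "calculate 95% confidence intervals for the difference in adjusted means".
- **Description of measurement data.** "The measurement data are tested for normality using the Shapiro–Wilk method". The result sets the summary statistics: mean and SD when normality holds, and only quartiles when it does not.
- **Basis for the between-arm method.** Secondary scale scores "will be analyzed using appropriate methods based on the type of indicator".
- **The tests named.** "quantitative information will be analyzed using analysis of variance or Wilcoxon rank sum test". Categorical and ordered data have their own tests in the next sentence.
- **Visits.** Under Secondary outcome, the three motor scales (MDS-UPDRS III, Mini-BES Test, 6MWT) are assessed as changes "from T0 to T1, T2, T3, and T4". The three non-motor scales (NMSS, MoCA, HAMD) are assessed as changes from T0 to T2, T3 and T4.

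**The concern.** ANOVA and the Wilcoxon rank sum test answer different questions. The first estimates a difference in means on the scale. The second asks whether values in one arm tend to be larger than in the other. A plan that names both for the same variables, without saying when each applies, leaves the estimand of every quantitative secondary comparison undecided until someone looks at the data.

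Two things follow. The choice can be influenced, even innocently, by the outcome data. And nothing requires the same test at successive visits of one scale, so a motor scale could be compared on means at T1 and on ranks at T3. A course over time built from such results is hard to read. The secondary objective is the effect of tACS on motor and non-motor symptoms, so these comparisons carry that objective.

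**Working it through.** **Step 1: is there a selection rule in the text?** The stated basis is the type of indicator. In {20a} that basis sorts data into quantitative, categorical and ordered. Both ANOVA and Wilcoxon sit inside the quantitative type, so this rule cannot choose between them. The only other criterion in the section that separates one quantitative measure from another is the Shapiro–Wilk result, and the sentence that contains it governs only how data are summarised. Either normality is the unstated gate or there is no gate. In both cases the choice is open when the data arrive.

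**Step 2: how often would one scale mix tests if normality were the gate?** The plan has no figure of its own on this point to reproduce.

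Inputs:
- From the Sample size section {14}: 30 per arm (27 / 0.9 = 30).
- From Secondary outcome: 4 post-baseline visits for motor scales, 3 for non-motor scales, so 3 × 4 + 3 × 3 = 21 contrasts.
- Assumed, not in the document: Shapiro–Wilk at 0.05 in each arm at each visit; Wilcoxon if either arm fails, otherwise ANOVA; gamma-shaped scores with skewness 0.63 to 1.0; between-visit correlation 0.5 to 0.85.

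Let q be the chance that one arm fails. A visit goes to Wilcoxon with probability p = 1 − (1 − q)². If k visits were independent, P(mixed) = 1 − (1 − p)^k − p^k.

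| Scores | q | p | P(mixed), 4 visits | P(mixed), 3 visits |
|---|---|---|---|---|
| Exactly normal | 0.05 | 1 − 0.95² = 0.098 | 1 − 0.9025⁴ − 0.0975⁴ = 0.34 | not needed |
| Skewness 0.63 | about 0.21 | 1 − 0.79² = 0.376 | 1 − 0.624⁴ − 0.376⁴ = 0.83 | 1 − 0.624³ − 0.376³ = 0.70 |
| Skewness 1.0 | about 0.44 | 1 − 0.56² = 0.686 | 1 − 0.314⁴ − 0.686⁴ = 0.77 | 1 − 0.314³ − 0.686³ = 0.65 |

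The q values for skewed scores are simulated. Correlation between visits lowers the mixing. Simulated with correlation 0.5 to 0.85:
- Four visits, skewness 0.63 to 1.0: 54–80%. Three visits: 44–67%.
- Four visits, exactly normal scores: 28–36%.
- Four visits, strongly skewed (lognormal) scores, correlation 0.6 or 0.8: under 1%, because the gate then nearly always picks Wilcoxon.
- Changes from T0, which is how the plan defines these outcomes: about 45–70% over four visits, somewhat lower over three.

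**Step 3: would it change conclusions or error rates?**
- With no true difference, the two-stage procedure rejected in 4.4–6.0% of simulated trials at one visit, against a nominal 5%.
- With a true difference of 0.5 SD (assumed), the two tests disagreed at P < 0.05 in about 8–11% of contrasts. If every contrast had such an effect, that is 0.08 × 21 = 1.7 to 0.11 × 21 = 2.3, so about 2 of 21.

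**The case against.** The strongest reply is that Shapiro–Wilk is used only to choose summary statistics, and that the document states a different basis for the test, the type of indicator. No sentence says that normality picks the test. None gives the unit of testing, its significance level, or whether arms are pooled. A reader might infer that a pretest decides the method scale by scale and visit by visit. The text does not say so, and the mixing rates above therefore describe an assumed rule. This part of the reply stands in full. What it does not do is supply a rule: without the normality gate, nothing chooses between the two tests.

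Other inferences that the document does not support:
- **Rank-tested results alone lack an effect estimate.** No estimate is named for secondary ANOVA comparisons either, and a condensed article may leave this to the analysis plan. The bare quartiles may likewise be a dropped median.
- **The t-tests in {20b} contradict {20a}.** They are post hoc and serve "to examine the improvements in all outcome variables through comparisons across different assessment time points", which is a different question from the between-arm test. Mean comparisons at this sample size also do not require normal scores.
- **Normality is checked on raw data instead of residuals.** The document does not say that arms are pooled. A check within each arm is already a residual check for a two-group ANOVA.
- **False positives are inflated.** The simulated rates stay close to 5%.

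It may also be said that the choice between the tests belongs in an analysis plan that is not shown. Had the article been silent, that would settle it. Here it states an alternative and leaves it unresolved, although it fixes the PDQ-39 analysis in the same paragraph.

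**Conclusion.** The point holds in limited form. For the quantitative secondary scales, {20a} names two tests with different targets and no usable rule for choosing, so the choice can be made after outcomes are seen and can differ between visits of one scale. That follows from the text alone.

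Its size depends on assumptions. If normality were tested per arm and per visit, with 30 per arm and mild to moderate skew, mixing within a scale would be common, very roughly 45–80% of trials. It would be about a third with exactly normal scores over four visits, and rare with strong skew. The loss is in consistency and interpretability of the secondary results. PDQ-39 is outside the problem because its model and interval are fixed.

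**What to change.** In {20a}, replace the ANOVA-or-Wilcoxon alternative with one analysis for each quantitative secondary scale, used at every visit whatever the distribution: the between-arm difference adjusted for the T0 value of that scale, from the same covariance model as PDQ-39, with its 95% CI. If residuals are skewed, obtain the interval by a robust or bootstrap method, so that the estimand does not change. Report Wilcoxon beside it as a sensitivity analysis. Use Shapiro–Wilk for description at most.

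The cost is a few sentences and no new data, since T0 values are already collected. Baseline adjustment should also improve precision. The downside is slightly less power for a strongly skewed scale, where the Wilcoxon sensitivity analysis gives a check.

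### Quantitative secondary scales are compared without their T0 score as covariate, and further covariates enter only on an undefined baseline difference: a moderate, avoidable loss of precision

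*Protocol article*

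**What the plan says.** Under Statistical methods for primary and secondary outcomes {20a}, the protocol article plans for PDQ-39 that "an analysis of covariance (ANOVA) model will be employed to estimate the adjusted means", with baseline taken into account and 95% confidence intervals for the difference in adjusted means. The secondary indicators "will be analyzed using appropriate methods based on the type of indicator", and then: "Component comparisons such as quantitative information will be analyzed using analysis of variance or Wilcoxon rank sum test". No baseline term is named for them. The same section also says: "Demographic and baseline characteristics of the two groups will be described and analyzed to assess comparability".

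The Outcomes section {12} defines the secondary endpoints as changes: "The secondary outcome will encompass changes in motor symptom scales". The motor scales are MDS-UPDRS III, Mini-BES Test and 6MWT; the non-motor scales are NMSS, MoCA and HAMD. The data collection section {18a} has all six measured at T0.

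Under Methods for additional analyses {20b}, adjustment is conditional: "In case of baseline differences between the 2 groups", the analyses will take account of "specific variables that may have influenced the results for subgroup analysis (e.g., LEDD, illness duration, and age". The section gives no rule for what counts as a difference. It also plans Bonferroni-corrected post hoc t-tests to "examine the improvements in all outcome variables through comparisons across different assessment time points".

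**The concern.** The T0 score is usually the strongest available predictor of a scale's later value. It is collected for all six secondary scales, yet used as a covariate for PDQ-39 only. With 27 to 30 patients per arm, leaving it out makes the secondary intervals wider than they need to be.

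The conditional rule is a second weakness. Under randomisation any baseline difference is due to chance, and a prognostic covariate improves precision whether or not it happens to be imbalanced. Without a stated criterion or a closed list, the covariates in the additional analyses are settled after the data have been seen.

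The post hoc comparisons across time points raise a smaller matter. Both arms receive MIRT, which the Discussion says improves quality of life by itself. A change over time within one arm therefore cannot be credited to tACS, and the plan does not say how such comparisons will be read.

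**Working it through.** **The plan's own figure.** The sample size section gives 27 per arm and 10% attrition: 27/(1 − 0.10) = 30, which reproduces. The 27 itself cannot be recomputed, because no effect size or SD is given. It was sized on PDQ-39, so this point does not touch it. It serves below only as the evaluable number per arm.

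**Assumptions.** The article gives no correlation r between T0 and follow-up, so r is varied. Variances at T0 and follow-up are taken as equal (σ²). The formulas describe the ANOVA option, not the rank-sum test.

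**Variance of the arm difference**, each relative to comparing raw follow-up scores:
- follow-up score: 1
- change from T0: 2(1 − r)
- ANCOVA on the T0 score: 1 − r²

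Hence ANCOVA relative to change is (1 − r²)/(2(1 − r)) = (1 + r)/2, and relative to follow-up it is 1 − r². The equivalent gain in patients is 1/ratio − 1.

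| r | ANCOVA ÷ change | equivalent gain | ANCOVA ÷ follow-up | equivalent gain |
|---|---|---|---|---|
| 0.5 | 0.75 | 33% | 0.75 | 33% |
| 0.6 | 0.80 | 25% | 0.64 | 56% |
| 0.7 | 0.85 | 18% | 0.51 | 96% |

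For the change score, intervals are wider than under ANCOVA by √(1/0.75) − 1 = 15%, √(1/0.80) − 1 = 12% and √(1/0.85) − 1 = 8%. Outside this range, the ratio to the change score is 0.65 at r = 0.3 and 0.95 at r = 0.9.

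**Power at 27 per arm**, for an assumed effect of 0.6 SD of the follow-up score, two-sided 5%, where v is the relative variance above: Φ(0.6·√(27/2)/√v − 1.96).
- r = 0.5: follow-up 0.60, change 0.60, ANCOVA 0.72
- r = 0.6: 0.60, 0.69, 0.79
- r = 0.7: 0.60, 0.81, 0.87

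To match ANCOVA with 27 per arm, a change-score ANOVA needs 27/0.75 = 36, 27/0.80 = 34 and 27/0.85 = 32 per arm.

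**The conditional rule.** The article states no trigger, so a baseline test at P < 0.05 was assumed, and the scale's own T0 score was used as the one candidate covariate. Simulation with 27 per arm (50,000 null runs, 30,000 runs at 0.6 SD), r = 0.5, 0.7, 0.8:
- Adjustment is triggered in about 5% of trials. With three independent covariates, at least one triggers in 1 − 0.95³ = 14%.
- Power for change scores is 0.58, 0.80, 0.93 both without adjustment and under the rule. Always using ANCOVA gives 0.70, 0.85, 0.95.
- Type I error under the rule is 0.044, 0.045, 0.047 for change scores and 0.042, 0.035, 0.031 for follow-up scores. Pre-specified ANCOVA stays at about 0.05.

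The rule therefore recovers almost none of the available precision and does not inflate the error rate.

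**The case against.** The best defence is that baseline is already in the secondary analysis, because the outcomes are changes from T0. That stands in large part. The statistics section speaks of scale scores, so the wording is not fully settled, but the change-score reading is the better supported one. A reader might infer that the plan ignores baseline and forgoes the equivalent of 56% to 96% more patients. Those figures apply only if raw follow-up scores are compared at r of 0.6 to 0.7.

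Second, the trigger sits under additional analyses and refers to subgroup analysis. A reader might infer that it makes the primary model data-driven. It does not: the baseline PDQ-39 term is planned unconditionally.

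Third, a reader might infer that normality testing selects between ANOVA and the rank test, or that within-arm tests will be used to claim a tACS effect. The text links Shapiro–Wilk only to how data are summarised. The time-point comparisons are called post hoc, are Bonferroni corrected, and come on top of planned between-group comparisons. Neither inference is established; the second needs only a clarifying sentence.

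Fourth, a condensed article may leave model terms to an analysis plan. That would answer a complaint about silence. Here the article names a method for the secondary scales and a condition for adjustment, and both can be improved as stated. The abbreviation slip in the PDQ-39 sentence (ANOVA after analysis of covariance) does not help, because the secondary sentence spells out its method.

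**Conclusion.** The point holds as a low-cost improvement to the secondary analyses. Using each scale's T0 value as a covariate would cut variance by 25%, 20% and 15% against a change-score ANOVA at assumed r of 0.5, 0.6 and 0.7. The saving reaches 36% to 49% only if follow-up scores are compared at r of 0.6 to 0.7. These sizes rest on the assumed correlations and on equal variances over time.

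The conditional covariate rule leaves the choice of covariates in the additional analyses dependent on the data and gains almost no precision. It should not be described as inflating type I error: under one fixed criterion the simulated rate was at or below 0.047. The undefined trigger and open list do leave room for choice after the fact, which a simulation of one fixed rule cannot measure. The primary PDQ-39 model and the sample size are not affected.

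**What to change.** Reword the statistics sections as follows.

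- Analyse each continuous secondary scale by ANCOVA with arm and that scale's own T0 value, reporting the between-arm difference and 95% CI at each visit for which the outcome is defined. Keep a rank-based analysis as a sensitivity check.
- Replace the baseline-difference trigger with a short covariate list fixed before unblinding and used regardless of observed imbalance, for example age and T0 LEDD. Illness duration can join if its collection is confirmed: {20b} names it, but the baseline list in {18a} does not. Keep the baseline comparison of the arms descriptive.
- State that comparisons across time points within an arm are descriptive, and that tACS effects are judged on between-arm differences.

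The cost is wording and one degree of freedom per covariate. No new patients or visits are needed, and the only data item to confirm is illness duration.
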